## Description of study days

Volunteers will be invited to participate in the trial by the study personnel. Recruitment will be conducted at a Training Centre of St. John ambulance, Vienna, Austria, before the starts of the lessons. After giving written informed consent, participants will be randomized using a web based randomization program

([www.random.org](http://www.random.org)) and allocated to perform standard CPR or CC only. The randomization for group allocation will be kept in opaque and sealed envelopes.

The evaluation will be performed with an independent investigator using a computer attached Resusci-Anne Skillreporter by Laerdal-Medical® and the Laerdal Skillreporter Software with Segstat (Version 2.3.0, Laerdal Medical, Stavanger, Norway).

The participants will be asked to perform BLS for five minutes on a manikin. The participants will then be asked to undertake any action they deem necessary to rescue the person simulated by the resuscitation manikin. Participants will not be informed about the underlying hypothesis or the outcome parameters. The room will be prepared to minimise outside interruptions.

Additionally, participants will be instructed to indicate the point in time during CPR when they feel that their fatigue is affecting the quality of the life support performed. ("During CPR and without stopping your actions, please tell us "NOW" when you perceive your fatigue is affecting the quality of the life support performed.)

Participants in both groups will receive one of the charts right at the beginning of the scenario with the information that "this chart will provide information on how to perform CPR" and with the start of the clock further instructions regarding its content. Both groups will not receive any further introduction or support. At the beginning of the scenario, the manikin will be positioned in a supine position on the floor. There will be no clock visible for the participant while performing CPR. An investigator is acting as bystander able to call the emergency medical service or to be sent to look for an automated external defibrillator (which will not be available in the scenario). Nonetheless, the investigator is instructed not to provide any information on how to perform CPR and does not physically take part in the primary check, CC, or mouth-to-mouth ventilations.

Data of steps performed or left out will be documented in hardcopy on the case report form by an investigator and the exact times and details of chest compressions and ventilations will be documented electronically (Laerdal Skillreporter Software with Segstat (Version 2.3.0, Laerdal Medical, Stavanger, Norway)). Checklists of necessary steps will be created based on the ERC BLS Guidelines 2010 in the same manner as published previously [Roessler *et al.* 2007, Koster *et al.* 2010].

After the five-minute period has ended, the participants will be informed that the emergency medical service is now taking over and that they can stop performing CPR. Directly thereafter, they will be asked the following questions "How exhausted are you now on a scale from 1 to 10, where 1 indicates no exhaustion at all and 10

maximum exhaustion?" (Lickert Like 1-10). If a participant choses to abort resuscitation attempts before the five minutes are over, the open-ended question "Why did you discontinue the resuscitation attempts?" will be raised.

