### **Methods:**

After consent of the Research Ethics Board of Medical University of Vienna and obtaining written informed consent of the participants, 84 medically untrained laypersons will be randomised to perform flow-chart assisted CPR for 300s following standard CPR guidelines or CC only CPR. The primary outcome parameter will be the total number of CC achieving the correct depth of 50-60mm. Secondary outcome parameters will be hands-off time, the total number of CC, and the compression rate. The total number of delivered rescue breaths, tidal volume, and time to deliver these will also be evaluated. Furthermore, the subjective point of exhaustion affecting the CPR quality, the reason for discontinuation of CPR if stopped within the 300sec. period and the exhaustion at the end of the CPR measures will be evaluated.

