## **Methodology**

### **Sample Size**

In order to detect a clinically important difference of 20% in compression depth with a power of 0.8 and a significance level set at 0.05, the sample size calculation yielded a total needed number of participants at 74. Since a drop out rate of approx. 10% must be expected 84 participants will be recruited. Data regarding compression depth utilizing standard CPR techniques in a manikin model ( $43 \pm 12$  mm) were provided by a previous publication and used to estimate the sample size [[name] *et al.* 2013]

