### Data management and calculations

Data will be described as absolute frequencies and percentages for categorical data and using mean and standard deviations (SD) for normally distributed data. All tests for p-values are two-sided and  $p \leq 0.05$  will be regarded to be statistically significant. Students t-test and chi-square test will be used as appropriate. As it is common practice, results of Likert-like scales will be treated as interval-measures and thereby analysed by using parametric tests [Norman *et al.* 2010, Cariio *et al.* 2008]. Local data management will be done using Microsoft Excel for Mac (Microsoft Corporation, USA) and R for Mac (R Foundation for Statistical Computing, Vienna, Austria) for statistical analysis. [R\_Development\_Core\_Team 2009] Graphics will be created using GraphPad Prism for Mac (GraphPad Software Inc., La Jolla, USA).

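### The NOW fatigue time may go unobserved (no fatigue by 300 s, or an earlier stop), yet the protocol names only the t-test and chi-square and has no rule for participants without a NOW

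*Protocol*

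**What the plan says.** The Methods part of the protocol abstract lists "the subjective point of exhaustion affecting the CPR quality" among the items to be evaluated. Under Description of study days it is captured as a moment: "participants will be instructed to indicate the point in time during CPR when they feel that their fatigue is affecting the quality", which they do by saying NOW aloud.

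The observation window is the same for all: "The participants will be asked to perform BLS for five minutes on a manikin". Earlier stopping is foreseen, because an open question on the reason is put "If a participant choses to abort resuscitation attempts before the five minutes are over".

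Data management and calculations gives the whole analysis: description "using mean and standard deviations (SD) for normally distributed data" or as frequencies and percentages, and "Students t-test and chi-square test will be used as appropriate". It argues for parametric tests on the Likert-like exhaustion score, but does not say which test applies to the NOW time.

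The protocol does not say what value a participant without a NOW receives. Nor does it say where the NOW time is written down. Electronic capture is described for compressions and ventilations, and the case report form for steps performed or left out.

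**The concern.** A time to fatigue observed for at most 300 s has two kinds of missing value: the participant who was not fatigued by the end, and the participant who stopped first without saying NOW. These lie at opposite ends of the fatigue scale, and neither named test accommodates a time that was not observed.

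If the test is run on whatever times were recorded, it is confined to reporters. Saying NOW happens after randomisation and depends on how tiring the arm is. The less tiring arm therefore loses more of its best performers, and the difference shrinks.

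The protocol's Background argues that fatigue erodes compression depth, and NOW is the only planned measure of when fatigue sets in. A diluted comparison here could be read as evidence against that argument. With no rule in the protocol, the coding could also be chosen after the data are seen.

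**Working it through.** **No figure to reproduce.** The protocol gives no expected fatigue time, effect or sample size for this outcome. Its sample size rests on compression depth ("clinically important difference of 20% in compression depth with a power of 0.8 and a significance level set at 0.05") and does not bear on this point.

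**Inputs from the protocol.** Window 300 s; 84 recruited; two-sided tests at 0.05.

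**Assumptions, not in the protocol.** 1:1 allocation (84/2 = 42 per arm); Weibull fatigue times with shape 2; scale b = 220 s in the more tiring arm and 300 s or 350 s in the other; nobody aborts.

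**Step 1: share reporting by 300 s.** F = 1 − exp[−(300/b)²].
- b = 220: 1 − exp(−1.860) = 0.844
- b = 300: 1 − exp(−1) = 0.632
- b = 350: 1 − exp(−0.735) = 0.520

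**Step 2: restricted mean time to 300 s, all participants.** R = b·(√π/2)·erf(300/b).
- b = 220: 194.97 × 0.9462 = 184.5 s
- b = 300: 265.87 × 0.8427 = 224.0 s
- b = 350: 310.18 × 0.7746 = 240.3 s

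**Step 3: mean among reporters only.** M = [R − 300(1 − F)]/F.
- b = 220: (184.5 − 46.7)/0.844 = 163.2 s
- b = 300: (224.0 − 110.4)/0.632 = 179.8 s
- b = 350: (240.3 − 143.9)/0.520 = 185.2 s

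**Step 4: what is lost.** For 220 against 300 s, the difference is about 40 s in all participants and about 17 s in reporters. For 220 against 350 s, it is about 56 s and 22 s.

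**Step 5: rejection rates by simulation, 42 per arm, 4000 runs.**

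| Scales (s) | t-test, reporters only | t-test, 300 s assigned | chi-square, NOW yes/no | log-rank |
|---|---|---|---|---|
| 220 vs 220 | 6% | 5% | 5% | 6% |
| 220 vs 260 | 9% | 23% | 22% | 26% |
| 220 vs 300 | 14% | 58% | 61% | 68% |
| 220 vs 350 | 20% | 87% | 90% | 93% |

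Repeat runs differ by about one percentage point, hence about 15% for the reporters-only test at 220 against 300 s.

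**Step 6: other assumptions.** Weibull shape 1.5, hazard ratio 2, 2000 runs, varying the share of the standard arm that never says NOW:

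| Never says NOW | t-test, reporters only | t-test, 300 s assigned | chi-square | log-rank |
|---|---|---|---|---|
| 10% | 61% | 83% | 47% | 86% |
| 30% | 25% | 76% | 73% | 82% |
| 50% | 10% | 61% | 68% | 70% |
| 70% | 6% | 42% | 54% | 52% |

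With no effect, all four reject in about 5–7% of runs. Assigning 300 s costs 3 to 10 points against log-rank. Chi-square is close to log-rank except when nearly everyone reports: at 10% it loses 86 − 47 = 39 points, because the information is then almost all in the timing.

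**Step 7: early stops.** If a participant stops from exhaustion at time a < 300 s without saying NOW and is assigned 300 s, the value is too long by 300 − a, and the arm mean rises by (300 − a)/42. The error is largest for those who gave out soonest, and it flatters the more tiring arm.

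**The case against.** A reader might infer that the plan drops or miscodes participants who never say NOW. The protocol does not say so. It names two tests to be used as appropriate, ties neither to this outcome, and neither excludes such participants nor assigns them a value. The reporters-only t-test is one possible reading.

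A reader might also infer that neither named test can use everyone. That is too strong. Chi-square on NOW yes/no keeps all participants, though it ignores timing. A t-test with 300 s assigned keeps all participants and all recorded times, and if nobody aborts it estimates the restricted mean difference itself. Steps 5 and 6 show that its cost is then modest and its type I error is held.

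Further, the fatigue times are assumed, the share of non-reporters is unknown, the outcome is not primary, and an analysis plan that is not shown might settle the coding.

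Most of this stands, and it limits the size of the point. It does not remove it. The protocol does choose tests in its own text, and neither is designed for times that go unobserved. The most favourable use of the t-test depends on nobody stopping without a NOW, while the protocol expects that some may stop.

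**Conclusion.** The point holds in a limited form. The NOW time is a secondary time-to-event outcome, unobserved when fatigue does not occur by 300 s or the participant stops first. The protocol offers only the t-test and chi-square, and no rule for a missing NOW.

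The size depends on the handling. In the 220 against 300 s illustration, dropping non-reporters cuts power from 68% to about 15% and the apparent difference from about 40 s to about 17 s. Keeping everyone with 300 s assigned, or with chi-square, leaves 58–61%. The severe loss is therefore a risk the wording allows, not a property of the stated plan. All of these figures rest on assumed Weibull times, 1:1 allocation and no aborts.

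Separately, assigning 300 s to someone who stopped from exhaustion would place the most fatigued among the least fatigued.

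Severity is low: one secondary outcome is affected, and the primary comparison is not.

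**What to change.** Add to Data management and calculations, and to the case report form:

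1. Record the NOW time in seconds from scenario start, together with any stop time and the reason for stopping.
2. Analyse all randomised participants in their allocated arm. Those who complete the scenario without a NOW are censored at 300 s.
3. Count stopping from exhaustion without a prior NOW as an event at the stop time. Censor stops for other reasons at the stop time.
4. Present Kaplan-Meier curves by arm, with a log-rank test, the difference in restricted mean time to 300 s, or both. Name in advance which is the main comparison.
5. Report the number per arm with a NOW, without a NOW at 300 s, and stopped early by reason.

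The cost is one field on the case report form, a few sentences of text and a little extra analysis in R, which is already the planned software. No more participants are needed.

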#### **Risk/benefit assessment:**

Apart from physical strain such as muscle pain or abrasion on the palm of the hand or knee after delivering chest compressions, there is no direct risk as the consequence of participation in the trial. To ensure participants added value, detailed information about the ERC CPR algorithm will be given after data collection. This information included written material on the 2010 CPR guidelines, or the 2015 CPR guidelines when available.

#### **Acknowledgement/approval of the study**

Before the start of the recruitment, the trial will be submitted for approval to the Research Ethics Board of Medical University of Vienna.

#### **Insurance**

No insurance necessary.

#### **Confidentiality**

All subject names will be kept secret in the investigator's files. Subjects will be identified throughout documentation and evaluation by the number allotted to them during the study. The subjects will be told that all study findings will be stored and handled in strictest confidence.

#### **Documentation of study findings**

All findings collected during the study will be entered on the case report forms provided by the Medical Simulation and Emergency Management Research Group, Department of General Anaesthesia and Intensive Care Medicine. All entries in the case report forms will be made legibly in black ink. If corrections are made to entries in the case report form, the words or figures will be ringed and a single stroke drawn through them. The correct value will be entered beside the old entry and the correction will be dated and initialled. Incorrect entries must not be covered with correcting fluid, or obliterated, or made illegible in any way.

#### **Publication of study results**

The findings of this study will be published by the investigators in a scientific journal and presented at scientific meetings. The manuscript will be circulated to all co-investigators before submission.

## **Authorship**

The principle investigator will be the first author, PD [name] [name]. Senior-, and corresponding author will be Assoc. [name]. [name]. Authorship will be granted for substantial contribution to the project. Supporting organisations will be acknowledged in the appropriate section of the final manuscript.

